### Measurement Instrument

A self-administered structured Web-based questionnaire was created based on review of both Swazi and international literature. For example, questions relating to sociodemographic characteristics were adopted from the 2007 Swaziland Demographic Health Survey, and those related to risky sexual behavior and intention to change behavior were developed from our formative studies. Additionally, the Perceived Risk of HIV Infection Scale (PRHS; found to have excellent internal consistency Cronbach alpha=0.88) [11] will be used to assess the primary outcome of this study. Past research has used a variety of approaches to measure HIV risk perception including single likelihood assessments [21,25]. The 8-item PRHS scale incorporates items assessing cognitive assessments of risk (eg, chance of infection), as well as intuitive assessments (eg, feeling vulnerable, worry, gut feeling about likelihood), and salience of risk (eg, thought about risk, can picture it happening) to provide a more comprehensive measure of perceived risk of HIV infection, thus our choice to use this scale. The questionnaire will be converted into a Web-based format accessible via a link. Detailed variables assessed by the questionnaire are described in the section below and the questionnaire is presented in Multimedia Appendix 2. The trial tools were piloted among respondents known to the principal investigator, who will not be part of the main trial, in order to assess Web-based eligibility screening functionality; user verification; participant randomization functionality; questionnaire skip logic functionality; and the average length of time it takes to complete the questionnaire.

#### Primary Outcome Measure

Adding one or more comparison groups to a pre- and post-intervention assessment will result in a stronger intervention design than having a single intervention group to a pre- and post-intervention assessment [26]. Therefore, the primary intervention outcome will be the change in HIV risk perception score from pre- to post-intervention assessment in the intervention group compared with the change in the wait-list control group. High perception is considered to be the first stage toward behavioral change and has been associated with HIV protective HIV behavior [27,28]. HIV risk perception using the PRHS will be used to measure the primary outcome at baseline and at 4-weeks follow-up.

#### Secondary Outcomes Measure

The secondary outcomes for this intervention are self-reported intention to have an HIV test; intention to reduce multiple concurrent sexual partnerships; and an increase in reported condom use in the last sexual encounter (Table 1).

**Table 1 table1:** Secondary outcome measures.

Measures		Baseline	Follow-up at 4 weeks
**Sexual reproductive history**			
	Condom use in the last sex	X^a^	X
	Number of sexual partners	X	X
**Intent to change behavior**			
	Intention to test for HIV and know partners’ HIV status	X	X
	Intention to reduce multiple concurrent partnerships	X	X
	Intention to use a condom	X	X
**Steady sexual partner’s history**			
	Has current sexual partner ever tested for HIV?	X	X
	Knowledge of current partner’s HIV status	X	X
**Demographics**			
	Age	X	
	Level of education	X	
	Employment status	X	
	Income level	X	
	Marital status	X	
	Ever tested for HIV	X	X
**Contact information**			
	Cellphone number and email	X	
**User experience**			
	Would you recommend the game to your friends?		X
	How did you hear about this game?		X
	Number of times player reached the end of the game		X
	Level of satisfaction about the game		X

^a^Timing of assessment.

### Data Collection Procedures

#### Baseline Data Collection

Participants will be recruited from Facebook users in Swaziland via a targeted Facebook advertisement. Potential participants will be directed to the study Web page where information about the intervention trial will be given and if willing, screening for eligibility will be done. After screening for eligibility, eligible individuals interested in participating in the trial will have an opportunity to ask detailed questions via free text message service offered by the WhatsApp app, Facebook messenger, or calling us. Sufficient time will be allowed for making an informed decision about participation in the study. Recruitment into this study will continue until our sample size is achieved.

After informed consent, a trial verification code will be sent to the participants via their mobile phones to prevent multiple identities in line with the CONSORT-EHEALTH guidelines 4a(ii) [29]. Upon confirmation of the unique verification code, participants will be enrolled in the trial and randomized into a control or intervention group. Subsequently, participants will be asked to answer the baseline Web-based questionnaire. In addition to study variables, contact information in the form of cellphone numbers will be collected at baseline to facilitate location of the research participants in the 1-month follow-up period [23,30]. The detailed questionnaire is outlined in Multimedia Appendix 2.

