**Methods:**

This is a two-arm randomized intervention trial. We will recruit 380 participants who meet the following eligibility criteria: 18-29 years of age, own a smartphone running an Android-based operating system, have the WhatsApp messaging app, live in Swaziland, and can adequately grant informed consent. Participants will be allocated into a smartphone interactive, educational story game, and a wait-list control group in a 1:1 allocation ratio. Subsequently, a self-administered Web-based questionnaire will be issued at baseline and after 4 weeks of exposure to the game. We hypothesize that the change in HIV risk perception between pre- and post-intervention assessment is greater in the intervention group compared with the change in the control group. Our primary hypothesis is based on the assumption that increased perceived risk of HIV provides cues to engage in protective behavior. Our primary outcome measure is HIV risk perceived mean change between pre- and post-intervention compared with the mean change in the wait-list control group at 4-weeks post-intervention. We will use standardized regression coefficients to calculate the effect of the intervention on our primary outcome with *P* values. We will conduct both intention to treat and as treated analysis.

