### Randomization

Upon confirmation of participants’ trial registration, participants will be assigned another unique code called “game unlock code,” which will be used for randomization using secure, remote, Web-based computer software within 24 hours of recruitment. As stated in the research design, participants will be randomized into 2 groups; the intervention group and the wait-list control group in a 1:1 ratio. The data analysis team will be blinded in this study, however, participants will not be blinded.

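### Unblinded participants are randomised before they complete the baseline questionnaire, so allocation can affect the baseline score that defines the primary change outcome

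*Protocol article*

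**What the plan says.** The Baseline Data Collection section gives the sequence as consent, verification code, randomisation, questionnaire. The trigger for randomisation is the code: "Upon confirmation of the unique verification code, participants will be enrolled in the trial and randomized". The next step is the baseline: participants are "randomized into a control or intervention group. Subsequently, participants will be asked to answer the baseline Web-based questionnaire".

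Two other places fit this order:

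- **Randomization.** A game unlock code is assigned once trial registration is confirmed, "which will be used for randomization using secure, remote, Web-based computer software within 24 hours of recruitment". A submitted questionnaire is not a condition.
- **Abstract, Methods.** Allocation is described first, followed by "Subsequently, a self-administered Web-based questionnaire will be issued at baseline" and again after 4 weeks.

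On blinding, the Randomization section states: "The data analysis team will be blinded in this study, however, participants will not be blinded".

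On the outcome, the Primary Outcome Measure section says "the primary intervention outcome will be the change in HIV risk perception score from pre- to post-intervention assessment", compared with the change in the wait-list arm. The scale is the 8-item PRHS, self-administered online. Under the statistical analysis of the primary outcome, the baseline score enters the mean change and is also a covariate in the adjusted regression.

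**The concern.** A baseline should be unaffected by treatment. Here it is recorded after allocation, by people who are not blinded, on a scale that covers worry, feelings of vulnerability and gut feeling. Such items could move when someone learns their arm or plays a game built to raise perceived risk. Study Design and Hypotheses also lets people download the game before they reach the trial website, so for some the app is already on the phone when the unlock code is assigned.

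Three uses of the baseline would be affected:

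- **Change score.** Any shift caused by allocation passes in full into the primary contrast.
- **Regression adjustment.** The covariate is itself measured after randomisation, so adjusting for it does not remove the bias.
- **Subgroups.** Hypothesis 2 concerns people reporting high-risk behaviour, and the Secondary Outcome Measures analysis takes those with low risk perception and no condom use. If membership is read from this baseline, it can depend on arm.

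There is also a loss problem. Someone randomised who never submits the baseline has no change score. Active tracing is described only for a missed 4-week assessment. A person told they are wait-listed may be less willing to fill in the form, so this loss could differ by arm and weaken the intention-to-treat comparison.

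**Working it through.** **Inputs from the article (Sample Size Calculation):** difference 0.477, SD 1.03, two-sided alpha 0.05, power 0.80, 1:1 allocation, 30% loss to follow-up, 380 in total.

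**Reproducing the planned size.** n per arm = 2 × [1.03 × (1.960 + 0.842) / 0.477]² = 73.2. This matches the stated 73 per arm (146 in total), or 74 if rounded up. The match requires 0.477 to be a raw difference in points; read as a standardised effect it gives 69. I therefore use 0.477 points.

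**Completers per arm.** 380 / 2 = 190, and 190 × 0.7 = 133.

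**Bias.** Let D be the true effect, and let d_I and d_C be the baseline shifts caused by allocation in the intervention and control arms.

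- Change-score contrast: D - (d_I - d_C). With a shift d in the intervention arm only, this is D - d.
- Follow-up score adjusted for baseline: about D - b × d, where b is the within-arm slope of follow-up on baseline.

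**Illustration (assumed; the article gives no figure).** 30% of the intervention arm opens the game first and already has the full effect.

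- d = 0.30 × 0.477 = 0.143.
- Change-score effect = 0.477 - 0.143 = 0.334, a fall of 30%. In SD units, 0.334 / 1.03 = 0.324.
- Standard error in SD units with 133 per arm = √(2/133) = 0.1226.
- Power = Φ(0.324/0.1226 - 1.96) = about 75%. With no shift, 0.463 SD gives 0.965, about 96%.
- Adjusted effect with b = 0.5 (assumed): 0.477 - 0.5 × 0.143 = 0.41.

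**Other shares, same formula, 133 per arm:** 5% early players gives about 95% power, 10% about 92%, 25% about 81%. Power falls below the planned 80% only when more than about a quarter of the arm already has the full effect.

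**Range of assumed shifts:**

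| d (points) | Expected estimate if D = 0.477 | Power, 73 per arm | Power, 133 per arm | Significant result if D = 0, 73 per arm | Significant result if D = 0, 133 per arm |
|---|---|---|---|---|---|
| 0 | 0.477 | 0.80 | 0.965 | 0.05 | 0.05 |
| 0.05 | 0.427 | 0.71 | 0.92 | 0.06 | 0.07 |
| 0.10 | 0.377 | 0.60 | 0.85 | 0.09 | 0.12 |
| 0.20 | 0.277 | 0.37 | 0.59 | 0.22 | 0.35 |
| 0.30 | 0.177 | 0.18 | 0.29 | 0.42 | 0.66 |

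The last two columns count significance in either direction. They matter mainly for a shift caused by knowing the allocation, since a game with no effect would not be expected to move the baseline through early play. The columns for 133 per arm correspond to the recruited sample after the planned loss.

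**The case against.** The strongest reply is that the article never says when participants learn their arm or when the unlock code opens the game.

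- Every registrant is assigned an unlock code, including those who become controls, so being assigned one does not mean that play is open. The survey runs on a separate verification code (Sampling Method). The two-code design is compatible with taking the baseline before the game is released.
- The first assessment is called pre-intervention throughout, which shows the intent.
- The CONSORT diagram (Figure 1) is not available here and might show a different order.
- The 30% scenario is severe, and early play biases towards no effect.
- Handling of missing baselines may be set out in an analysis plan that is not shown.

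Most of this stands as a limit on certainty and size. Contamination is possible, not demonstrated, and small shares of early players cost little power. How far missing baselines damage the intention-to-treat analysis depends on a method not given here.

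It does not answer the main point. The order is stated outright, participants are unblinded, and no sentence makes disclosure or release wait for the questionnaire. Separate codes permit a safe sequence but do not require one. The bias need not be towards the null either: a reaction to being wait-listed would move the control baseline, in a direction that cannot be known in advance.

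**Conclusion.** The concern holds. Followed as written, the plan collects the baseline of its primary outcome after unblinded allocation, so allocation can alter that baseline and randomised people can be lost before they have one.

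The change-score bias equals the difference in baseline shift between arms, with sign reversed. The adjusted analysis carries a reduced share of it, about half if the slope is 0.5. No shift can be estimated from the article. The illustrative loss from about 96% to 75% power rests on three things: the assumed 30% of early players, their having the full effect at once, and the article's SD of 1.03 applying to the change. Smaller shares give much smaller losses.

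The case for changing the plan does not depend on that example. Once people are enrolled in this order, analysis cannot recover a baseline free of allocation effects, and prevention before launch costs almost nothing.

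**What to change.** Reorder the web flow: eligibility, consent, verification code, submitted baseline questionnaire, randomisation, then disclosure of the arm and release of the unlock code. The randomised set is then, by construction, those who submitted a baseline, and the target of 380 counts those people. Rewrite the Abstract Methods, Randomization and Baseline Data Collection sections together so that all three state this order, and check Figure 1 against it.

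If randomisation must stay at code confirmation, the minimum is to conceal both the arm and the unlock code until the questionnaire is submitted, and to say so. If the web system already does this, the article should state it.

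The cost is re-sequencing some web pages and repeating the functionality pilot. The article gives the trial's status as pre-initiation, so no data are affected. The sample size calculation is unchanged. Some people will drop out before randomisation instead of after it, which does not bias the comparison between arms.

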#### Four-Weeks Follow-Up Data Collection

Trial participants will be followed-up for 4 weeks, the game will collect log data and send this data to our servers when the participant goes on the Internet, this will allow us to assess the exposure to the intervention without over burdening our participants to manually send us their usage data. Data captured will be limited to login data. In addition to this, a Web-based questionnaire will be sent to participants at the end of the follow-up period. Participants who will miss their 4-week follow-up assessment will be actively traced though phone calls and text messages.

### Data Management and Statistical Analysis

#### Data Quality Assurance

First, Web-based questionnaires must be usable even for less experienced and knowledgeable Internet users [31], therefore we will exploit specific technical possibilities offered by open source Web-based questionnaires, such as visually highlighting buttons and predefined input fields. Additionally, we will use help features and input checks to assist participants when filling out the Web-based questionnaire. Beyond this, we will pilot test all filters and instructions given in the questionnaire. Second, to limit undesired multiple participation [32], either at baseline assessment or follow-up assessment, “sessions” will be used together with a verification code that participants will receive upon giving informed consent. Third, a specific problem that is faced by Web-based surveys is that respondents may “click through” the questionnaire, a phenomenon that becomes apparent when the interview is completed in less than the theoretical minimum time [31], therefore, the responses will be checked for plausibility and consistency and inconsistent records will be documented and censored from the final analysis.

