### Sample Size Calculation

The trial will be powered on the primary outcome measure and based on comparison of the change in HIV risk perception score from pre- to post-intervention assessment in the intervention group at 4 weeks. A study conducted in Uganda estimated mean HIV risk perception of M=3.27, SD *=* 1.03, therefore, we used this estimation as our baseline mean and SD to calculate our effect size [21]. Assuming a moderate effect size of 0.477 (identified by Chu et al [22]), alpha (two-tailed)=0.05, beta=0.20, with 1:1 allocation ratio between both groups, and a SD of the outcome in the population of 1.03, the total sample required to sufficiently power the study would be 146 (73 for each group). Moreover, assuming a 30% loss to follow-up rate [15], we then inflated the sample by 30% to yield a sample of 190. After that, we considered gender differences and once more inflated the sample by a factor of 2 to give a final sample size of 380. Finally, to ensure a balance between males and females in both groups we will recruit 190 females and 190 males. The sample size was calculated using Web-based sample size calculation software [23,24].

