#### Primary Outcome Measure: HIV Risk Perception Score

First, we will use bivariate analysis to calculate the mean between baselines and follow-up. Next, to estimate the difference between the 2 groups, we will calculate the difference between the mean change of the intervention group and the mean change of the wait-list control group using two-sample paired *t* test. We will not perform interim analysis.

Secondly, in the case that, even after randomization, we observe some baseline differences, we will use multiple linear regression to adjust for those differences; where the outcome will be the follow-up score and the independent variables will be the intervention group, baseline scores, age, gender, marital status, level of education employment status, current monthly income, and number of times players played SwaziYolo. We will present our results in standardized regression coefficients for the intervention effect on the outcome variable as previously done for this type of hypothesis [25].

Although great effort will be put to minimize attrition, it is common for eHealth trials to typically have substantial attrition [26]. For this reason, our primary outcome analysis will prioritize analysis of the subjects who adhered to their group assignment and were sufficiently exposed to the intervention. Therefore, both pre-protocol analysis (as treated analysis) as well as intention to treat analysis will be done and both results will be reported. The approach of conducting both “intention to treat analysis” together with “as treated analysis” has been observed in literature for example, Weinstein and colleagues [33] followed this approach in their randomized trial comparing surgical versus nonoperative treatment for lumbar disk herniation.

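### Click-through or inconsistent records are dropped from the final analysis after randomisation, which does not fit the promised intention-to-treat analysis and could bias it

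*Protocol article*

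**What the plan says.** Four statements in the protocol article bear on this.

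- **Data Quality Assurance** notes that web respondents may click through a questionnaire, "a phenomenon that becomes apparent when the interview is completed in less than the theoretical minimum time". It then gives the rule: "the responses will be checked for plausibility and consistency and inconsistent records will be documented and censored from the final analysis". The rule applies to the final analysis without qualification.
- **Baseline Data Collection** sets the order of steps. Once the verification code is confirmed, "participants will be enrolled in the trial and randomized into a control or intervention group". The next sentence reads: "Subsequently, participants will be asked to answer the baseline Web-based questionnaire".
- **Primary Outcome Measure: HIV Risk Perception Score** plans a per-protocol (as-treated) analysis, "as well as intention to treat analysis will be done and both results will be reported". It makes no exception for records that fail the quality check. It also gives priority to participants who adhered and were sufficiently exposed.
- **Randomization** states: "The data analysis team will be blinded in this study, however, participants will not be blinded".

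**The concern.** An intention-to-treat comparison is protected by randomisation only as long as nothing that happens after allocation decides whose data count. Here a data-quality screen applied after allocation does decide that, and by its wording it covers the intention-to-treat analysis too.

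The screen could act differently in the two arms. Participants are not blinded, and only the intervention arm plays the game before the 4-week questionnaire. The game aims to shift the risk perception, intentions and behaviour that the questionnaire asks about. It could therefore affect how carefully people answer and how well their answers at the two time points agree.

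The stake is higher because the analysis given priority is already selected on adherence and exposure. The intention-to-treat result is the only planned comparison that could keep the randomised groups intact. If the same records leave it, neither planned analysis uses the observed outcomes as randomised.

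**Working it through.** **1. Are the removals post-randomisation?** The order in Baseline Data Collection is consent, verification code, enrolment and randomisation, baseline questionnaire, then follow-up at 4 weeks. Both questionnaires come after randomisation, so any record the rule can remove belongs to a randomised participant.

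**2. The planned effect, from the plan's own figure.** Inputs from Sample Size Calculation: effect 0.477, SD 1.03, and "alpha (two-tailed)=0.05, beta=0.20, with 1:1 allocation ratio between both groups". Reading 0.477 as a raw difference in score points:

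n per group = 2 × [1.03 × (1.960 + 0.842) / 0.477]² = 73.2

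This agrees with the stated 73 per group (146 in total). Reading 0.477 as a standardised effect gives 69 per group, which does not. The planned effect in SD units is therefore 0.477 / 1.03 = 0.463. The 1.03 is taken as the SD of the change, as the plan's own calculation does.

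**3. Formula for the bias.** Let f be the fraction of records removed in an arm and δ the mean change in kept records minus that in removed records, in SD units. The full-arm mean is (1 − f) × kept mean + f × removed mean, so

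kept mean = full-arm mean + f × δ

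and the bias in the between-arm difference is f₁δ₁ − f₀δ₀. With the same δ in both arms this is δ × (f₁ − f₀). It is zero when rates and gaps are equal. Its sign follows from which arm loses more records and which responders they are.

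**4. Size.** The article gives neither rates nor gaps, so all rates and gaps below are assumptions.

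| Removed, game v control | δ (SD) | Bias (SD) | Share of 0.463 |
|---|---|---|---|
| 10% v 10% | 1.0 | 0 | 0% |
| 10% v 5% | 0.5 | 0.5 × 0.05 = 0.025 | 5% |
| 15% v 5% | 1.0 | 1.0 × 0.10 = 0.10 | 22% |

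**5. Effect on false positives if the game does nothing.** With 380 randomised and 30% lost, 190 × 0.70 = 133 per arm remain before removal.

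- 10% v 5% leaves 119.7 and 126.35. SE = √(1/119.7 + 1/126.35) = 0.1275 SD, so bias/SE = 0.025 / 0.1275 = 0.196. Two-sided type I error is 1 − Φ(1.960 − 0.196) + Φ(−1.960 − 0.196) = 5.4%.
- 15% v 5% leaves 113.05 and 126.35. SE = 0.1295 SD, so bias/SE = 0.10 / 0.1295 = 0.772, and type I error is 12.1%.

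**6. Power.** For a difference of 0.477 with SD 1.03, power at 133 per arm is 96.5%. It is 94.8% if a further 10% of records are removed, and 92.2% if 20% are.

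**The case against.** The strongest reply is that the rule speaks of records, not people. A reader might infer that randomised participants are struck from the intention-to-treat set, so that the two sections flatly contradict each other. The article does not say that. Censoring could mean setting an invalid response to missing while the participant stays in the set under the allocated arm, and an article may leave the handling of missing data to a fuller document. This stands as a limit on the wording. It does not dispose of the point: on either reading, observed outcomes of randomised participants leave the final analysis, and the rule as written covers both planned analyses.

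A second reply is that click-through answers do not measure risk perception, so keeping them has a cost. This also stands. If, by assumption, 10% of records in each arm were noise with no mean change, the effect would shrink by 10%, about 0.046 SD, which exceeds the milder bias above. Simply keeping all flagged values in a single main analysis would therefore be a poor remedy.

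Third, the analysts are blinded and removals are to be documented. These safeguards limit selective removal by the team. They do not prevent the two arms from answering differently.

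Fourth, the larger scenario is demanding. A 1 SD gap is more than twice the planned effect, and it is combined with a 10-point difference in removal rates.

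Two further inferences go beyond the text. Participants are unblinded, but the article does not say whether they learn their arm before the baseline questionnaire, so arm-dependent answering at baseline is not established. And the removals do not threaten the overall sample size.

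**Conclusion.** The point holds in limited form. The data-quality rule removes data after randomisation, is not confined to the as-treated analysis, and does not fit the promised intention-to-treat analysis; the two sections need to be reconciled. A reader might conclude that the trial will be biased by it. The documents support only that it could be, if removal differs by arm in rate or in the kind of responder removed.

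The range of 0.025 to 0.10 SD rests on assumed removal rates, a common gap in both arms, and 0.477 read as a raw difference. The lower end is the more believable, and the bias could run in either direction. The change should be made, because the trial has not started and the remedy is cheap.

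**What to change.** 1. **Order of steps (Baseline Data Collection).** Have participants complete the baseline questionnaire, and check it, before randomisation. Unusable baseline records are then screened out before allocation, without bias. Cost: one reordered web step.

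2. **Wording (Data Quality Assurance).** Replace the removal from the final analysis with text to this effect: *Records are flagged by a completion-time and consistency rule that is fixed before unblinding and applied without knowledge of arm. Every randomised participant stays in the intention-to-treat set. The intention-to-treat result is reported twice: with flagged follow-up responses as recorded, and with them treated as missing under a stated method. The numbers flagged are reported by arm.* Cost: a change of wording and one extra analysis.

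The downside is that the version keeping flagged responses is noisier and may be somewhat diluted. Reporting both versions shows how far the conclusion depends on the flagged records.
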